### Sample size calculation

The total sample size will be 72 participants. This number was calculated to provide an 80% power (α = 0.05) with an effect size of 0.14. The number of patients per group was determined using a sample size calculation with G*Power 3.1.9.7. The sample was calculated for two groups, and 8 measurements will be performed: at baseline, during the IUD insertion phases (Pozzi, hysterometry, and IUD placement), at 5 and 15 minutes after placement, and at 24 and 48 hours after the procedure.

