### Inclusion and exclusion criteria

The study will include women aged 18–50, with no restrictions on race or socioeconomic status. Both nulliparous and multiparous women will be considered eligible, provided they meet other criteria established to ensure the safety and appropriateness of the IUD placement procedure.

Conversely, women with suspected or confirmed pregnancy, a history of diagnosed chronic pain, or active pelvic infection will be excluded from the study. Women who took pain medication within 12 hours before the procedure will be excluded to prevent interference with pain perception. Women with known contraindications for IUD placement, such as significant uterine cavity distortion, active pelvic inflammatory disease, or Wilson’s disease, will be deemed ineligible [4]. Other exclusion criteria include copper allergy, unexplained abnormal uterine bleeding [4], a history of photosensitivity, or any condition affecting the lumbar region, such as active neoplasms, established osteomyelitis, or pre-existing deep tissue injuries with necrosis or infection. The participants will not be permitted to participate in any other clinical study during the trial.

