### Collection of patient history and risk factors

The patient history will be collected from all participants using a questionnaire. In addition to general demographic data (age, sex, marital status, occupation, educational level, and income), the medical history will cover chief complaints, current disease status, past medical history, medications in use, smoking, alcohol consumption, the use of systemic antibiotic therapy in the previous 12 months, hospitalization or infection (including skin infections) in the previous 12 months, previous IUD use, and preferred contraceptive methods. This questionnaire will enable the correlation of clinical, demographic, and epidemiological risk factors with the study outcomes in this population.

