#### Secondary outcomes.

Pain description – Free narrative reportNumber of analgesics taken – Paracetamol intake recorded from baseline to 48 hours after T 380 copper IUD placement.Anxiety – Assessed using the Generalized Anxiety Disorder 7 (GAD-7) questionnaire [15] 15 minutes after IUD placement.Quality of life – Measured using the WHOQOL-Pain instrument [16] from baseline to 48 hours after placement.Patient satisfaction – Assessed through close-ended questions [6] 15 minutes after placement.Time required for relief of abdominal discomfort (menstrual cramps) – Measured in days from baseline.Verification of successful placement – Investigated dichotomously (success/failure) from baseline to 48 hours after placement.Adverse effects – Including uterine perforation, IUD displacement, abdominal pain, increased vaginal bleeding, and allergic reactions. An open-ended question will be used for the participants to report adverse effects, followed by a list of potential impacts to help them recall any unreported symptoms.Side effects – including cramps, mild pain, light bleeding, and tongue numbness. An open-ended question will be asked first, followed by a list of potential side effects to improve recall.

*Primary outcome – Pain - Visual Analog Scale (VAS)*: Pain will be assessed using the Visual Analog Scale (VAS), as illustrated below. One end of the scale is marked “0”, corresponding to the absence of pain, and the other end is marked “10”, indicating unbearable pain. The same scale will be used for all participants. The same operator will always provide instructions for marking the scale. Pain scores will be recorded, and this assessment will be performed at all study visits, including during the IUD insertion phases (Pozzi, hysterometry, and IUD placement), at 5 and 15 minutes after placement, and at 24 and 48 hours after the procedure. The participants will be asked about spontaneous pain at three distinct moments during placement: pain during clamping with the Pozzi forceps, pain during hysterometry (uterine length measurement), and pain during the actual IUD placement. All participants will receive daily phone call reminders to ensure accurate recording of their outcomes [17].

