*Secondary outcome – Anxiety assessment*: Anxiety levels in patients undergoing T 380 copper IUD placement for contraception will be assessed using the seven-item Generalized Anxiety Disorder (GAD-7) questionnaire administered at baseline and 15 minutes after the procedure [15]. The GAD-7 is a self-report instrument designed to assess generalized anxiety symptoms based on the DSM-IV diagnostic criteria. The questionnaire consists of seven items measuring the frequency of anxiety-related issues over the previous two weeks, using a 4-point Likert scale: 0 = Never, 1 = Several days, 2 = More than half the days, 3 = Almost every day. The GAD-7 can be administered in clinical and research settings, both in person and online, and takes approximately five minutes to complete. The total score ranges from 0 to 21 points, with higher scores indicating greater severity of anxiety symptoms. Classification is divided into four categories: scores from 0 to 4 indicate no anxiety, 5–9 correspond to mild anxiety, 10–14 correspond to moderate anxiety, and 15–21 indicate severe anxiety. The GAD-7 has strong validity and reliability and is widely used in clinical and non-clinical populations. Depending on the application context, it can be analyzed using a unifactorial or bifactorial model (somatic and cognitive-emotional items).

*Secondary outcome – Assessment of quality of life using the WHOQOL-Pain instrument at baseline and 24 hours after the procedure*: The WHOQOL-Pain is an additional module of the WHOQOL-100 specifically developed to assess quality of life in individuals living with chronic pain. Following a preliminary study, ten new facets related to pain and discomfort were identified, four of which were selected for the final version of the instrument: Pain Relief; Anger and Frustration; Vulnerability, Fear and Concern; and Uncertainty [16]. Each facet comprises four questions that address different dimensions of the pain experience. The responses are recorded on a five-point Likert scale to measure intensity, capacity, evaluation, and frequency. The scores are converted to a 0–100 scale, enabling the quantitative interpretation of pain levels and the impact on quality of life. The WHOQOL-Pain items are not integrated into the WHOQOL-100 and are applied separately at the end of the main questionnaire. This structure facilitates the individualized analysis of pain-related facets, enabling a specific, detailed assessment of physical chronic pain experiences.

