### Statistical analysis

Statistical analysis will be performed using the Statistical Package for the Social Sciences (SPSS) version 24.0 or equivalent software package. The significance level will be set at 5% (p < 0.05) for all tests. Data normality will be determined using the Shapiro-Wilk test. Continuous variables will be reported as either the mean and standard deviation or the median and interquartile range, depending on the distribution of the data. Categorical variables will be expressed as absolute and relative frequencies. For comparisons between the experimental group (active PBM) and control group (sham PBM), the Mann-Whitney test will be used for continuous variables with non-normal distribution. When the expected minimum value is less than 5, categorical variables will be compared using either the chi-square test or Fisher’s exact test. The analysis of pain-related variables (intensity measured by the Visual Analog Scale [VAS]) at different time points (baseline, during placement, 5 and 15 minutes, and 24 hours after the procedure) will be conducted using the Friedman test. As the primary outcome will be measured repeatedly over time, the analysis will account for the within-subject correlation inherent to this repeated-measures design.

For the measures of anxiety (GAD-7), quality of life (WHOQOL-100), and satisfaction with the procedure, the Mann-Whitney test will be used to compare groups across assessment time points. The use of post-procedural analgesics will be compared between groups using repeated-measures analysis of variance (ANOVA). No interim analyses or stopping guidelines are planned due to the short duration of the trial and low risk.

Missing data will be assessed for frequency and pattern. In the event of missing values, the analyses will be performed using the available data, and the extent of missingness will be reported. If necessary, appropriate statistical methods will be applied depending on the nature and proportion of the missing data.

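### Anxiety and quality of life are compared by an unadjusted Mann-Whitney test although baseline scores are to be collected: valid, but precision is given away at no saving

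*Protocol article*

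**What the plan says.** All references are to the Protocol article.

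- **Measurement.** The paragraph on anxiety assessment has the GAD-7 "questionnaire administered at baseline and 15 minutes after the procedure". The paragraph on quality of life places WHOQOL-Pain at baseline and 24 hours after the procedure.
- **Outcome list.** The list that opens Secondary outcomes gives anxiety by the GAD-7 "questionnaire [15] 15 minutes after IUD placement", with no baseline. It also runs quality of life from baseline to 48 hours, not 24.
- **Analysis.** For anxiety, quality of life and satisfaction, Statistical analysis states that "the Mann-Whitney test will be used to compare groups across assessment time points". It names no covariate, change score or other use of baseline for these outcomes. It calls the quality-of-life instrument WHOQOL-100, while the outcome sections call it WHOQOL-Pain. I read the sentence as applying to WHOQOL-Pain.
- **Pain.** VAS is not in that sentence. It goes to a Friedman test over time points that include baseline, with a general statement that within-subject correlation will be accounted for.
- **Size.** "The total sample size will be 72 participants", which is 36 per group.

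**The concern.** A pre-treatment measurement of the same scale is usually the best single predictor of the follow-up score. Adjusting for it removes outcome variance unrelated to treatment and corrects any chance difference between the arms at the start. A Mann-Whitney test of the follow-up scores does neither. With 36 women per arm, power for moderate effects on secondary outcomes is limited from the outset, so the precision lost could decide whether a real difference is seen.

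The conflict over GAD-7 timing makes this more pressing. An analysis can be changed later, but a baseline questionnaire that was never given cannot be recovered.

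**Working it through.** **1. The plan's own figure.** The sample size section says: "This number was calculated to provide an 80% power (α = 0.05) with an effect size of 0.14". It adds: "The sample was calculated for two groups, and 8 measurements will be performed: at baseline, during the IUD insertion phases". Reading 0.14 as Cohen's f in a repeated-measures group-by-time test (2 groups, 8 measurements, sphericity), the required total is 94 at a within-woman correlation of 0, 76 at 0.2, 72 at about 0.23 to 0.24, 66 at 0.3 and 48 at 0.5. The correlation used is not stated, so 72 can be neither confirmed nor called wrong. It is a calculation for pain and gives no target effect for GAD-7 or WHOQOL-Pain. Only the 36 per arm carries forward.

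**2. Inputs.**
- n = 36 per arm: document.
- Significance level 5%: document. Two-sided is my assumption.
- True difference d = 0.5 SD, with 0.2 SD as a sensitivity case: assumed.
- Correlation r between baseline and follow-up score, 0.3 to 0.7: assumed.

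**3. Formulas.** Unadjusted: noncentrality = d × √(n/2), with 2n − 2 = 70 degrees of freedom. Baseline-adjusted (ANCOVA): the residual variance is multiplied by 1 − r², so noncentrality = d × √(n/2) / √(1 − r²), with 69 degrees of freedom. Power comes from the noncentral t distribution; the critical value is 1.99 in both cases.

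**4. Numbers in.** √(36/2) = 4.243, so at d = 0.5 the unadjusted noncentrality is 2.12. The equivalent total is 72 / (1 − r²).

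| Analysis | 1 − r² | Noncentrality, d = 0.5 | Power, d = 0.5 | Power, d = 0.2 | Equivalent unadjusted total |
|---|---|---|---|---|---|
| Unadjusted | 1 | 2.12 | 55% | 13% | 72 |
| Adjusted, r = 0.3 | 0.91 | 2.22 | 59% | 14% | 79 |
| Adjusted, r = 0.5 | 0.75 | 2.45 | 68% | 16% | 96 |
| Adjusted, r = 0.7 | 0.51 | 2.97 | 83% | 22% | 141 |

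**5. Does this carry over to rank tests?** The table uses t-type tests. In simulations with normal data at 0.67 SD, where the unadjusted t-test has 80% power, the Mann-Whitney test had about 78%. Rank-based ANCOVA had 82%, 88% and 96% at r = 0.3, 0.5 and 0.7, against about 84%, 90% and 97% for ordinary ANCOVA. Most of the gain is kept on ranks.

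**6. Pain, for comparison.** Women with diagnosed chronic pain are excluded, so many baseline VAS scores may be near 0. With an assumed 85% of zeros and an observed correlation of about 0.20 to 0.33, adjusting for baseline VAS raised simulated power at 0.67 SD only to 82–83%, from a nominal 80%.

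**The case against.** The strongest reply is that nothing here is an error. An unadjusted Mann-Whitney test is valid in a randomised trial, and its type I error rate already allows for chance imbalance. The document never promises adjustment, and covariates are often left to an analysis plan, which is not shown. Validity stands, so this is a matter of efficiency only. The appeal to an unseen plan is weaker: the article names the test, and that test cannot use scores the trial sets out to collect.

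The gain may also be overstated for GAD-7. The instrument asks about the previous two weeks and is repeated 15 minutes after the procedure. That overlap makes a high correlation plausible, but it also makes a 0.5 SD treatment effect doubtful. This stands. At 0.2 SD, even r = 0.7 lifts power only from 13% to 22%, and adjustment does not cure the recall window.

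A reader might infer three stronger points that the document does not support:

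- **That pain is analysed by the same unadjusted test.** The sentence does not cover VAS. The absence of a named active-versus-sham model for pain is a separate matter. The likely gain from baseline VAS is small.
- **That parity could not be adjusted for.** The eligibility text says "Both nulliparous and multiparous women will be considered eligible", and the history items, which end with "previous IUD use, and preferred contraceptive methods", do not name parity. But that is a condensed list that includes past medical history, and the form itself is not shown. Silence there proves nothing.
- **That a significance test at baseline is planned.** The wording about assessment time points permits that reading but does not state it.

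**Conclusion.** The point holds for GAD-7 and WHOQOL-Pain. Baseline scores are to be collected, the named test sets them aside, and one of the two statements of GAD-7 timing would remove the baseline score altogether. The consequence is lost precision, not bias or an invalid test.

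At an assumed 0.5 SD difference, the power forgone is about 4 percentage points at a baseline correlation of 0.3, 13 at 0.5 and 28 at 0.7. The gain is material from a correlation of about 0.5. Neither the effect nor the correlation is in the document, and for GAD-7 the true effect may well be smaller. The document does not support extending the finding to the primary pain outcome or to parity.

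**What to change.** 1. **Statistical analysis:** compare follow-up GAD-7 (15 minutes) and WHOQOL-Pain between groups by ANCOVA with the baseline score as covariate, on ranks if the scores are skewed. State that between-group tests are made at post-treatment time points only.
2. **Secondary outcomes:** reconcile the outcome list with the anxiety paragraph so that baseline GAD-7 is kept. At the same time settle the quality-of-life time point (24 or 48 hours) and the instrument name (WHOQOL-Pain or WHOQOL-100), so that the adjusted analysis has one defined outcome.
3. **Optional:** any between-group model for VAS may include baseline VAS and baseline GAD-7 as prespecified covariates, with a small expected gain. First reconcile the Allocation section, which opens the envelope and applies PBM immediately after placement, with the description of PBM as preventive. This decides whether the VAS scores taken during insertion come before or after treatment.

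The cost is a few lines of wording and one degree of freedom per outcome. No extra women or visits are needed. The baseline GAD-7, about five minutes to complete, is already in the anxiety paragraph. The article lists the trial as not yet recruiting, so the change can be made before any data are seen.

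### The plan promises to analyse the available data, but the Friedman test for VAS and the repeated-measures ANOVA for tablets keep only women with a complete row, so a missed 24 h score discards observed clinic pain scores

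*Protocol article*

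**What the plan says.** All of the relevant text is in the Statistical analysis section of the protocol article, unless noted.

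- **Missing data.** The rule is that "the analyses will be performed using the available data, and the extent of missingness will be reported". A further sentence allows other methods if they prove necessary, chosen "depending on the nature and proportion of the missing data".
- **VAS, the primary outcome.** The analysis over time "will be conducted using the Friedman test". The readings listed for it are "baseline, during placement, 5 and 15 minutes, and 24 hours after the procedure". The 48 h reading is not in that list, although the Sample size calculation and Primary outcome sections both include it.
- **Within-woman correlation.** The section adds that "the analysis will account for the within-subject correlation inherent to this repeated-measures design", but names no method for this beyond the Friedman test.
- **Tablets.** Paracetamol use is to be compared between arms by repeated-measures ANOVA. The Secondary outcomes section records it at 24 and 48 h.
- **Other comparisons.** Mann-Whitney is named for comparing the arms on non-normal continuous variables.

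**The concern.** The Friedman test ranks each woman's readings against one another, so it needs all of them. Classical repeated-measures ANOVA likewise drops a woman who lacks any level of the repeated factor. Neither can use a partly observed row. A rule of analysing what is available therefore sits beside two methods that set aside available values.

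The consequence is awkward for this trial. The question is pain during placement, and those scores are taken in the clinic with the woman present. In the named VAS analysis their use depends on a score recorded a day later. The later readings look the most exposed to loss. The article relies on daily telephone reminders, and the only dated return visit is at 30 days, so recording at home is a fair inference. It is still an inference, because the article also speaks of study visits and follow-up visits. What is at stake is precision in a trial where 72 is both the number calculated and the number to be randomised.

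**Working it through.** **Inputs from the article.** 72 women, 36 per arm (Sample size calculation; Allocation). The VAS row has seven readings if placement means its three phases: baseline, Pozzi, hysterometry, IUD placement, 5 min, 15 min and 24 h. Six are taken in the clinic and one later. The tablet row has two counts, at 24 and 48 h.

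**Assumed inputs.** The article gives neither a missing rate nor a VAS standard deviation. The missing rate q at 24 h is taken as 5%, 10% or 20%, with clinic scores complete. The SD is taken as 2.5 cm.

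**Step 1: does the Friedman test drop the row?** In a simulated table of 72 women by 7 readings, seven women had the last reading deleted. The Friedman statistic with missing values omitted was 0.5802, identical to the statistic on the 65 complete rows. The 7 × 6 = 42 clinic scores that were present played no part. For repeated-measures ANOVA the same follows from the form of the method; it was not simulated.

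**Step 2: women lost from the VAS row as written.** Expected loss = 72 × q.

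| q | Women lost | Women kept | Clinic scores discarded (6 × women lost) |
|---|---|---|---|
| 5% | 3.6, about 4 | 68.4 | 21.6, about 22 |
| 10% | 7.2, about 7 | 64.8 | 43.2, about 43 |
| 20% | 14.4, about 14 | 57.6 | 86.4, about 86 |

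A missed 48 h score costs nothing here, because 48 h is not in the list. It would do so only if 48 h were added to match the other two sections.

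**Step 3: cost in precision.** For an arm difference in means with equal arms and N women in total, SE = SD × √(4/N).

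- No loss: 2.5 × √(4/72) = 0.59
- q = 5%: 2.5 × √(4/68.4) = 0.60
- q = 10%: 2.5 × √(4/64.8) = 0.62
- q = 20%: 2.5 × √(4/57.6) = 0.66

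This is a yardstick for an arm comparison restricted to the retained women. It is not a Friedman result, because that test produces no arm difference.

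**Step 4: tablets.** A woman with one count but not the other is dropped and her observed count is lost. How often this happens depends on whether the two counts go missing together. If they always do, no observed count is discarded. No single figure can be given from the article.

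**The case against.** Several points on the other side are sound.

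- **Wording.** The rule does not say that all available data will be used. It can be read as no imputation, with each test run on the cases it can take. So this is a rule the named tests serve poorly, not a flat contradiction in words.
- **Mann-Whitney.** If the arms are compared on VAS one time point at a time by this test, every observed clinic score is kept. The loss is confined to the repeated-measures analysis.
- **Follow-up may be nearly complete.** Daily reminders and checks of missing values against source records are planned. With few missing scores the loss is small.
- **Tablets.** Each woman logs tablets with date and time, so both counts come from one record and would often be present or absent together. This weakens the tablet half of the point, which concerns a secondary outcome.
- **The open-ended fallback.** A reader might fault the plan for not naming its other methods. Such detail is commonly left to a statistical analysis plan or the full protocol, neither of which is shown, so it is not raised here. Nor does it repair the mismatch, because the named tests stay as they are.

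Two stronger readings are tempting but unsupported. The first is that row deletion biases the treatment effect on insertion pain. The Friedman test has no arm term, so no named analysis yields an arm contrast on the retained rows, and nothing in the article shows which women would fail to report. The second is that missing 24 h and 48 h readings compound for VAS. The list stops at 24 h, so as written they do not.

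**Conclusion.** The point holds in a limited form. The stated missing-data rule and the two named repeated-measures methods do not fit together, and following the plan as written would discard observed clinic pain scores from the repeated-measures analysis of the primary outcome. Under the assumed missing rates and SD, the standard error of an arm difference on the retained women would be about 3%, 5% or 12% larger (√(72/68.4) = 1.03, √(72/64.8) = 1.05, √(72/57.6) = 1.12). It would be smaller still if 24 h reporting is nearly complete. For tablets the mismatch is real in principle but its size is unknown. It is worth correcting because the remedy is cheap and the discarded scores are those that bear on the trial's question.

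**What to change.** **VAS.** Replace the Friedman test with one linear mixed model, fitted by REML to every observed post-baseline reading. Include arm, reading, arm-by-reading and baseline VAS, with a stated covariance for readings within a woman. A woman without a late score then still contributes her clinic scores. State at the same time whether 48 h is among the readings, so that the section agrees with the Sample size calculation and Primary outcome sections.

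**Tablets.** Replace repeated-measures ANOVA with a likelihood-based count mixed model, for example negative binomial, that keeps women with either the 24 h or the 48 h count.

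**Cost.** Analysis wording only, with no extra women or data. The small downside is that a covariance structure must be stated and a model replaces a simple rank test. These models use the observed readings fully, but they do not correct for missingness that depends on the unseen scores themselves. If the named tests are kept, the minimum change is to say plainly that they are complete-case analyses.
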